### Health economics

Cost-effectiveness analyses will be performed, by comparing the healthcare costs between the midwife-assisted RM group, the PSM group, and the CG. Cost-effectiveness analyses are reliable and validated methods for health economic evaluation, and will allow us to estimate whether midwife-assisted RM is desirable relative to current prenatal follow-up. The following aspects will be evaluated in PREMOM II: (1) the incremental cost of midwife-assisted RM to society and (2) the incremental health effects for the pregnant women. The incremental costs will be calculated by comparing the costs of the medical procedures and medications between the CG (women who receive conventional prenatal follow-up) and the midwife-assisted RM group. The difference represents the incremental costs of midwife-assisted RM. Information on healthcare costs will be collected for women in all six study groups from the IMA database. The incremental cost of the health effects will be calculated as the difference in health effects between the CG, PSM group, and midwife-assisted RM group. Relevant health effects will be identified from a validated set of effects using associated questionnaires developed by the International Consortium for Health Outcomes Measurements (ICHOM). We will also assess willingness to pay, by measuring how much pregnant women would like to pay for prenatal follow-up involving RM.

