### Health economic considerations

The PREMOM I study also considered the health economics of RM for pregnant women in the 2015 and 2016 groups. RM enabled an average cost reduction for the Belgian National Health Care System of €740.39 per pregnancy (14.89%; 2015 data) up to €1950.37 per pregnancy (2015 + 2016 data). This cost saving was due to the reduction in prenatal visits, prenatal admissions, and neonatal admissions to the NICU [23, 24]. The savings were mostly related to neonatal care, particularly for neonates born at a gestational age of < 34 weeks, with a total cost reduction of €9123.16 per pregnancy in the RM group relative to the CG group. The cost reduction per pregnancy in the RM group versus the CG group was €225.86 for neonates born between 34 and 37 weeks and €35.93 for neonates born after 37 weeks. The finding that the main costs savings are driven by reduced neonatal care is not surprising since neonatal care is particularly intensive and is one of the most expensive forms of in-hospital care [25]. GHD-related neonatal morbidities include complications of prematurity, and the severity of prematurity is correlated with the cost of neonatal care [26]. Since the publication of those articles, we are not aware of additional health economic analyses of RM in pregnancy. Furthermore, there are few reports covering similar topics in non-pregnant patients.

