### Sample size calculations

Sample size calculations were performed by Censtat (Hasselt University, [name], [name]) to detect clinically meaningful differences between the midwife-assisted RM group and the CG in women with GHD, for two key factors (1) gestational age for neonates born before 34 weeks and (2) admission to the prenatal ward for neonates born after 34 weeks, based on previous work.
Gestational age for neonates born before 34 weeks: a difference of ≥10 days between the midwife-assisted RM group and the CG was observed in our pilot studies, and was used as a clinically relevant difference for the power calculation. Priority was given to this sample size calculation because each 1-day increase in gestational age at birth has a significant impact on the neonate’s short- and long-term outcomesAdmission to the prenatal ward of neonates born after 34 weeks: a proportional difference of 20% between the midwife-assisted RM group and the CG was considered clinically relevant. This outcome was expected to be most frequent in the PSM group, followed by the CG group, and less likely in the RM group.

The sample size calculations are based on summary statistics derived from our pilot study. A power of 80% and a significance level of 1.67% was used. A within-center variance of 6 (for gestational age) and a random intercept standard deviation of 0.0875 (for prenatal ward admission) was assumed. To obtain 80% power, we estimated that ≥168 GHD pregnancies with delivery before the gestational age of 34 weeks and ≥ 360 GHD pregnancies admitted to the prenatal ward after 34 weeks would need to be included in the study. At each center, the women will be equally divided into the three study groups.

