### Stakeholder experiences

In the three study groups, we will use PROMs to map the effectiveness and impact of RM, as estimated by the pregnant woman. The PROMs listed in Table 2 will be included in this study. Each of the PROMs will be measured using a validated questionnaire. Additionally, as PROMs recommended by ICHOM, the investigators will include EQ-5D-5L questionnaires.

**Table 2 Tab2:** Overview of patient-reported outcomes

PROM	Questionnaire
Quality of Life	EuroQoL EQ-5D-5L
Mental Health	ICHOM (Patient Health Questionnaire 2)
Satisfaction with care	ICHOM
Healthcare responsiveness	ICHOM
Birth experience	ICHOM (Birth Satisfaction Scale – Revised)

The questionnaires listed in Table 2 will be collected via a single questionnaire that will take up to 10 min to complete.

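### The cost-effectiveness analysis defines its health effects for the pregnant women only and names no neonatal effect, although the trial's priority endpoint is neonatal

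*Protocol article*

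**What the plan says.** The Health economics section of the protocol article lists two aspects for evaluation: "the incremental cost of midwife-assisted RM to society and (2) the incremental health effects for the pregnant women". It gives the source of the effects: "Relevant health effects will be identified from a validated set of effects using associated questionnaires developed by the International Consortium for Health Outcomes Measurements (ICHOM"). It states the purpose of the analysis, which "will allow us to estimate whether midwife-assisted RM is desirable relative to current prenatal follow-up". A later sentence in the same section reads: "The incremental cost of the health effects will be calculated as the difference in health effects between the CG, PSM group, and midwife-assisted RM group". On costs it says: "Information on healthcare costs will be collected for women in all six study groups from the IMA database". The Data collection section adds that these costs span the prenatal, perinatal and postnatal periods.

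The Stakeholder experiences section says of the questionnaires that "we will use PROMs to map the effectiveness and impact of RM, as estimated by the pregnant woman". Table 2 lists quality of life, mental health, satisfaction with care, healthcare responsiveness and birth experience.

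Elsewhere the newborn is central. Under Sample size calculations, the first of two key factors is gestational age in births before 34 weeks, with a relevant difference of at least 10 days: "Priority was given to this sample size calculation because each 1-day increase in gestational age at birth has a significant impact" on the newborn's outcomes. Primary outcome measures include gestational age at delivery, APGAR, birth weight, complications, NICU hospitalization and length of stay. The Discussion expects fewer NICU admissions with midwife-assisted RM.

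**The concern.** The two sides of the economic comparison do not cover the same people. Costs are taken from the viewpoint of society, while effects are those of the mother. The benefit to which the trial gives sample-size priority, later birth in the earliest deliveries, and the NICU admissions it hopes to avoid, fall on the newborn. Neither is named on the effect side.

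At stake is what the economic analysis can say about whether RM is desirable. If RM improves neonatal outcomes and leaves the mothers' effects unchanged, the effect difference as defined is zero. A reader of the economic results alone would see no health gain beside the cost difference, even if the trial had achieved its main neonatal aim.

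**Working it through.** The article gives no figure for this analysis, so there is none to reproduce. The check sets the definitions side by side and follows them through.

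**1. Who is counted where**

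| Element | Section | Mother | Newborn |
|---|---|---|---|
| Incremental health effects | Health economics | named | not named |
| Questionnaire topics | Stakeholder experiences, Table 2 | all five reported by the woman | none |
| Priority sample-size factor | Sample size calculations | – | gestational age, births before 34 weeks |
| Primary outcomes | Primary outcome measures | prenatal and delivery data | neonatal data, including NICU stay |
| Hypothesis on outcomes | Discussion | fewer inductions, fewer PE diagnoses | fewer NICU admissions |
| Costs | Health economics; Data collection | named | possible (perinatal and postnatal care), not spelled out |

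The neonatal outcomes are therefore collected, but the economic section does not carry them to the effect side.

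**2. What the definition does**

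Write the incremental effect as defined as ΔE = ΔE(mother). Write the incremental cost as ΔC = ΔC(RM programme) + ΔC(mother's care) + ΔC(newborn's care), where the last term enters only if the insurance data include the newborn. Let g be the gain in gestational age.

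- If ΔE(mother) = 0, then ΔE = 0 for every value of g, including the planned 10 days, and for any number of NICU admissions avoided. A ratio ΔC/ΔE has no value.
- If newborn costs are included, the gain can still show as a negative ΔC(newborn's care). RM could then look cheaper with no health effect, or dearer with no health effect, depending on the programme cost.
- If newborn costs are not included, the gain appears on neither side.

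**3. Size of the effect left out, on the plan's own figures**

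The sample-size section plans 168 births before 34 weeks among 3741 women before dropout: 168/3741 = 0.0449, or 4.5%. The relevant difference in that group is at least 10 days. As an illustration, suppose the gain is exactly 10 days, arises only in that group, and the group is the same share of each arm. The mean gain over all randomised women is then 0.0449 × 10 = 0.45 days. So the omitted effect is large for a few women and small on average.

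**4. Background on cost only**

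The Health economic considerations section says of PREMOM I: "The savings were mostly related to neonatal care, particularly for neonates born at a gestational age of" under 34 weeks. Weighting its three savings by the Flemish shares of GHD deliveries in the Background gives 0.066 × 9123.16 + 0.133 × 225.86 + 0.801 × 35.93 = 602.13 + 30.04 + 28.78 = EUR 660.95 per GHD pregnancy. Against the two reported totals this is 660.95/740.39 = 89% or 660.95/1950.37 = 34%. The weights are not those of the PREMOM I sample, and the sum is a cost. It does not measure the missing health effect and is not used in the conclusion.

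**The case against.** The case for leaving the text alone has several parts.

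- **The contents of the ICHOM set are not shown.** It may hold neonatal items, and Table 2 sits under stakeholder experiences, not as the effect list of the economic analysis. This stands as far as it goes: one cannot say that Table 2 is the whole list. But the section itself names the women as those whose effects count, so the restriction is stated and not merely left to a fuller plan.
- **The harm is contained.** The economics is a secondary outcome, and gestational age and NICU stay will be reported as primary outcomes in any case. This stands, and it limits the weight of the point.
- **The phrase about the cost of health effects is a slip.** The same sentence defines it as a difference in effects. This stands; the correction is editorial.

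Three stronger readings are tempting, and the documents do not support them.

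- A reader might infer a rule that would declare RM ineffective. No threshold, ratio or decision rule is stated; the section lists aspects to be evaluated.
- A reader might infer that newborn costs are left out. The cost data extend to perinatal and postnatal care, and the Discussion ties expected costs to perinatal outcomes. Which records are requested is a detail that an article may leave to the full plan, so confirmation is all that is needed.
- A reader might infer that most of PREMOM II's expected savings are neonatal. That statement describes PREMOM I. For PREMOM II the hypothesis is only that midwife-assisted RM will not raise costs relative to conventional care.

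**Conclusion.** The point holds for the effect side of the secondary cost-effectiveness analysis. As defined, it omits the health gain to which the trial gives sample-size priority and the NICU admissions it expects to avoid. With unchanged maternal effects, the whole neonatal gain counts as zero.

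This rests on reading the named beneficiary literally and on the ICHOM set not bringing in neonatal effects by another route. It does not show that RM would be judged not worthwhile, that neonatal savings would be lost, or that the clinical conclusions are affected. The correction is cheap and worth making before the economic analysis is run.

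**What to change.** In the Health economics section, widen the second aspect so that it covers health effects for the women and their newborns. Next to the maternal measure, report two results built on outcomes already collected:

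- incremental cost per NICU admission avoided;
- incremental cost per day of gestation gained.

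Compute both across all randomised women, not only among births before 34 weeks, since membership of that group is itself an outcome. Count fetal or neonatal death as an unfavourable result, so that a death does not pass as an avoided admission or as gestation gained. Because the average gain may be well under a day, show the cost and effect differences beside each ratio.

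Confirm that costs are summed over mother and newborn for each randomised woman, and name the newborns' records in the insurance data request if they are not already there. Editorially, call the difference in health effects an incremental health effect, not an incremental cost.

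The cost is a little more analysis and more than one ratio to interpret. If the investigators prefer to keep the effect side maternal, they should say so and give the reason.

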#### Midwife-assisted RM group

Pregnant women allocated to the midwife-assisted RM group will also receive a blood pressure monitor, as used in the PSM group, and will be asked to measure their blood pressure twice daily. They will also register their body weight every week in the app. The data will be sent to the hospital for review by the allocated midwife. The midwife will contact the responsible obstetrician if any abnormal values are detected allowing interventions to be performed if necessary, or when the pregnant woman doesn’t take her vital parameters for more than 48 h. This study group is identical to that in PREMOM I.

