### Data collection

Data on background variables, obstetric outcomes, and neonatal outcomes after delivery will be collected from the electronic patient files recorded at each hospital. Data on blood pressure and the associated compliance rate will be collected from DHARMA, an online platform developed by the Mobile Health Unit (Limburg Clinical Research Center, Hasselt University – ZOL - Jessa). Information about healthcare costs of pre-, peri-, and postnatal care will be collected from the Intermutualistisch Agentschap (IMA) health insurance database [41]. Information about the PROMs will be recorded using validated questionnaires.

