Our first hypothesis is that women in the midwife-assisted RM group will have lower numbers of prenatal consultations and unplanned hospital visits compared with the PSM group and the CG. We also believe that women in the PSM group will have the greatest healthcare consumption because their vital signs are not being reviewed by a healthcare professional and no one is able to provide them with specific advice or interpretations, so these women are likely to seek clinical support. Our second hypothesis is that the gestational outcomes will be improved in the midwife-assisted RM group as a consequence of fewer inductions, a greater number of spontaneous deliveries, fewer admissions to an NICU, and fewer diagnoses of PE relative to the CG. We expect that the outcomes of the CG and the PSM group will be the same because the women in these groups are not supervised by a healthcare worker. Related to the previous hypothesis, our next hypothesis is that midwife-assisted RM will not lead to an increase in costs to the healthcare system relative to conventional prenatal care in the CG, and that healthcare costs will be greater in the PSM group than in the CG. These expectations are based on the expected prenatal follow-up and the perinatal outcomes because interventions incur costs and negative gestational outcomes are expensive, and likely to exceed the cost of RM itself. Our penultimate hypothesis is that the number of interventions will be greatest in the midwife-assisted RM group, followed by the PSM group, and the CG. This assumption considers that the timely interventions will result in fewer evolutions of GHD to PE, leading to improved perinatal outcomes in the midwife-assisted RM group. This effect is expected to be smallest in the CG. We also think that appropriate adjustment of antihypertensive medications will result in improved outcomes. Our final hypothesis is that the midwife-assisted RM group will be associated with the most positive stakeholder perceptions, followed by the PSM group. The CG is expected to report the least positive perceptions.

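### The stated incremental-cost rule leaves out any cost of delivering remote monitoring that is not billed to the insurer, which can only favour remote monitoring

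*Protocol article*

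**What the plan says.** The Health economics section names as its first target "the incremental cost of midwife-assisted RM to society". It then gives the computing rule: "The incremental costs will be calculated by comparing the costs of the medical procedures and medications between the CG" and the midwife-assisted RM group. It closes the definition with "The difference represents the incremental costs of midwife-assisted RM".

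On data, the same section says: "Information on healthcare costs will be collected for women in all six study groups from the IMA database". The Data collection section agrees: "Information about healthcare costs of pre-, peri-, and postnatal care will be collected from the Intermutualistisch Agentschap (IMA) health insurance database". The article names no other cost source.

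The group descriptions show what RM consumes. Women in the RM group "will also receive a blood pressure monitor, as used in the PSM group", and "The data will be sent to the hospital for review by the allocated midwife", who contacts the obstetrician about abnormal values or missed measurements. Data collection names an online platform for the blood pressure data. Women in the CG get no RM devices. The primary outcomes include the number of contacts with women and with obstetricians.

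The Discussion hypothesises that RM will not raise healthcare-system costs relative to the CG. It argues that interventions and poor outcomes are expensive and "likely to exceed the cost of RM itself".

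**The concern.** The rule defines the incremental cost of RM through categories in which RM's own resources do not obviously appear. A study-supplied monitor, a data platform and a midwife's review of incoming readings are not, on a plain reading, medical procedures or medications, and nothing says they generate insurance claims. To the extent that they do not, the rule measures the care that RM avoids or triggers and leaves out what RM costs to run.

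That does not match the Discussion, whose argument sets savings against the cost of RM. Testing it needs both sides of that balance. The perspective is also inconsistent: society in the aim, the healthcare system in the hypothesis, and insurer data in the source.

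The cost results are meant to help persuade hospital administrators and government to adopt RM. An incremental cost that leaves out part of the programme they would fund would mislead them, in RM's favour.

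**Working it through.** The article reports no planned cost figure to reproduce, so the check is algebraic, followed by a range.

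**Direction of the bias.** Let

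- D = mean cost of procedures and medications in RM minus the same in CG (the rule in Health economics);
- c = per-woman cost of delivering RM that is not in claims, with c ≥ 0. CG women receive no RM devices, and monitoring is not part of their care, so their corresponding cost is taken as zero.

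Full incremental cost = D + c. The rule reports D, so its error is D − (D + c) = −c. The sign is fixed: RM always looks cheaper than it is, by c.

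For the other contrasts, let p be the unbilled delivery cost per woman in the PSM group, who receive the same monitor and whose data are stored. The same rule would understate PSM vs CG by p and RM vs PSM by c − p. In the last contrast the device cost cancels, leaving mainly midwife review and data handling.

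**Size.** The article gives no value for c. The values below are assumptions. They are set against the two average pilot savings per pregnancy in the Background section on health economics: €740.39 (2015 data) and €1950.37 (2015 and 2016 data). The saving left is the pilot saving minus c.

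| Assumed c | c / 740.39 | Saving left from €740.39 | c / 1950.37 | Saving left from €1950.37 |
|---|---|---|---|---|
| €200 | 27% | €540.39 | 10% | €1750.37 |
| €500 | 68% | €240.39 | 26% | €1450.37 |
| €800 | 108% | −€59.61 | 41% | €1150.37 |

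The sign changes only when c exceeds the saving: above €740.39 on the lower figure and above €1950.37 on the higher. Within the assumed range this happens once, at €800 against the lower figure.

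**A limit on this table.** The article attributes the pilot savings to fewer prenatal visits, prenatal admissions and NICU admissions. It does not say whether RM's cost had already been subtracted. If it had, subtracting c again would count it twice. The pilot figures therefore serve only as a yardstick for how large c might be relative to a plausible saving.

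**The case against.** The strongest reply is that this is a condensed article. Itemised resources and unit costs usually sit in a fuller protocol or health-economic plan, and the text never says that only procedures and medications count. The Discussion shows that the authors know RM has a cost, and the logged contacts could be used to price it. This would succeed if the article were merely silent. It is not: it gives a definition and equates the result with the incremental cost of RM. Followed as written, that definition yields a figure without the unbilled delivery cost.

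Other parts of the reply stand:

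- A reader might infer that RM is priced at zero. The article does not support that. It does not say which RM activities are billed, and any billed part is already in claims. Consultations and admissions prompted by RM would be expected to appear there.
- A reader might infer that the expected saving would vanish. That is not shown. It depends on an unknown c, and against the higher pilot saving none of the assumed costs changes the sign.
- The pilot saving of only €35.93 for births after 37 weeks, beside the Background's 80.1% of GHD deliveries at that stage, invites the claim that a trivial programme cost reverses the result for most women. That joins a pilot stratum to the Flanders-wide mix of GHD deliveries, which is not the randomised population.
- The contacts are logged as counts, not staff minutes, and routine data review without a contact is not listed. Staff time therefore cannot simply be read off the trial data.
- Society in the stated aim is a matter of one word, since the hypothesis already speaks of the healthcare system.

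**Conclusion.** The concern holds in this limited form. The rule in Health economics understates the incremental cost of midwife-assisted RM by whatever part of its delivery cost is not billed to the insurer, and the error always favours RM. It also conflicts with the societal aim in the same section and with the Discussion's balancing of savings against RM's cost.

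The direction rests on two premises: the insurance database is the only named cost source, and the CG bears no RM delivery cost. The size is unknown. It could be negligible if most RM activity is billed. At the assumed €200 to €800 per woman it is 27% to 108% of the lower pilot saving, or 10% to 41% of the higher, subject to the doubt about whether those savings are already net. Cost analysis is a secondary outcome, so the sample size and the clinical comparisons are unaffected. The wording should be corrected before the cost analysis is run.

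**What to change.** Replace the definition in Health economics with: incremental cost = difference in claims cost + difference in per-woman delivery cost not already in claims. Then:

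1. List the delivery components for RM and for PSM: devices, platform and, where applicable, midwife and obstetrician time. State which, if any, are billed, so that nothing is counted twice.
2. Estimate staff time from the logged contacts, with an assumed time per contact and for routine data review. Report a sensitivity range for these assumptions and for unit costs.
3. Apply the same definition to RM vs CG, PSM vs CG and RM vs PSM.
4. State the perspective as the healthcare system, matching the hypothesis in the Discussion, instead of society. An insurer-only label would not fit, because the article does not say that the insurer bears the device, platform or midwife costs.

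The cost is a small amount of extra costing work, including time assumptions that the trial does not record directly, and a less favourable apparent saving. Randomisation and clinical care do not change.
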